### Study design

The study will employ a within-subject, randomized, double-blind, and sham-controlled design. Clinical eligibility, including the dyslexia assessment, the neuropsychological assessment, and the psychopathological assessment will be evaluated on Day 0 (Baseline). Participants will be exposed to three conditions (Day 1, Day 2, Day 3): (A) a single active tDCS session; (B) a single active hf-tRNS session; and (C) a single sham tDCS or sham hf-tRNS session. Each condition will be separated from the other by a one-week interval to avoid carry-over effects (27). The ordering of conditions will be counter-matched among participants. After recruitment, participants will be allocated to one of six possible combinations of conditions (i.e., ABC, ACB, BAC, BCA, CBA or CAB). Stratified randomization will be performed by an independent researcher immediately after the participant completes the screening evaluation. This process will ensure assignment masking. Stratified randomization will use the minimal sufficient balancing method to prevent imbalances in baseline characteristics and will take into account participants’ demographics (e.g., age, IQ, and gender) and the severity of DD (calculated as the mean standard deviation between speed and accuracy in the text reading task) (45–48). The randomization information will be retained by an independent researcher until the data collection has been completed (Figure 1).

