### Sham tES conditions

To control for potential placebo effects, participants during the sham condition will undergo the same procedures as those in the active conditions (active tDCS, active hf-tRNS). This includes using the same electrode positioning and tRNS/tDCS equipment turn-on time (30 s). Apart from this short stimulation, during the sham condition participants will not receive the real stimulation (0 mA) for the rest of the session.

Among all participants, half of them will undergo a sham tDCS session (with the same electrode positioning and tDCS equipment turn-on time), while the other half will undergo a sham tRNS session (with the same electrode positioning and tRNS equipment turn-on time).

All participants, their families and the evaluators will be blinded to the stimulation conditions.

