### Safety, tolerability, and blinding assessment

Adverse effects will be assessed using a questionnaire adapted from Antal et al. (59). Participants will be asked to complete the questionnaire after each session. The questionnaire includes items related to potential adverse effects such as headache, tingling, skin redness, neck pain, scalp pain, itching, drowsiness, difficulty concentrating, burning sensation, and acute mood change. In addition, other information regarding when the adverse event occurred, its duration, and where the discomfort is located will be recorded. Participants will quantify the severity of adverse effects as follows: (0) absent; (1) mild; (2) moderate; and (3) severe.

The questionnaire will also inquire about participants’ perception of whether they received active stimulation or not. For more details, see Supplementary materials S4.

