### Statistical analyses and expected results

The Shapiro–Wilk test will be used to test the normality of the data and Levene’s test for the homogeneity of variances. When data will be normally distributed and the assumption of homogeneity will not be violated, parametric analyses will be computed. When one assumption will not be met, non-parametric tests will be conducted or a log-transformation of the distribution will be applied. Sphericity will be verified by Mauchly’s sphericity test and when not met, Greenhouse–Geisser correction will be applied.

Chi-Square analyses will be used to compare the groups on demographic and safety and blinding measures (categorical variables).

Covarying for age, a preliminary analysis to test the effect of the four repetitions (Day 0, Day 1, Day 2, and Day 3) of the reading tasks (accuracy and speed of TEXT, HF, LF, and NW) will be conducted.

RM-ANOVA will be used to compare reading measures (TEXT, HF, LF, and NW accuracy and speed), separately, with conditions (Day 0, A, B, C) as a within-subjects factor and age as covariate.

*Post hoc* comparisons will be assessed using Tukey’s honest significance test.

Partial eta squares (η_p_^2^) will be used as measures of effect sizes.

We hypothesize that:

hf-tRNS will be at least as effective as tDCS in improving TEXT reading accuracy compared with sham condition (primary outcome);hf-tRNS and tDCS will improve performance in the remaining reading tasks (TEXT reading speed and HF, LF, and NW reading accuracy and speed) compared with sham condition;hf-tRNS and tDCS will be as safe as sham condition (i.e., neither tDCS nor hf-tRNS will induce severe AEs or lead to dropouts due to intolerance to stimulation);the blinding will be kept across the conditions.

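### Safety and blinding answers are paired within child, but the protocol assigns them to chi-square tests between groups; the resulting p-values are invalid, and the direction of error depends on the within-child correlation

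*Protocol article*

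**What the plan says.** All references are to the protocol article.

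- **Study design:** "The study will employ a within-subject, randomized, double-blind, and sham-controlled design". "Participants will be exposed to three conditions (Day 1, Day 2, Day 3"), namely active tDCS, active hf-tRNS and one sham session.
- **Safety, tolerability, and blinding assessment:** "Participants will be asked to complete the questionnaire after each session". Severity is ordinal: "Participants will quantify the severity of adverse effects as follows: (0) absent; (1) mild; (2) moderate; and (3) severe". The same form covers blinding: "The questionnaire will also inquire about participants’ perception of whether they received active stimulation or not".
- **Statistical analyses and expected results:** "Chi-Square analyses will be used to compare the groups on demographic and safety and blinding measures (categorical variables"). No paired categorical test is named. The reading outcomes, in the same section, do get a repeated-measures ANOVA with condition as a within-subject factor.
- **Sham tES conditions:** "Among all participants, half of them will undergo a sham tDCS session", and the other half a sham tRNS session. Besides the six sequences, sham type is the only split between children.

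The hypotheses include safety equal to sham, explained as "neither tDCS nor hf-tRNS will induce severe AEs or lead to dropouts due to intolerance to stimulation", and blinding maintained across conditions. The Discussion counts the comparison of tDCS and tRNS on safety and tolerability among the study's main purposes.

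**The concern.** The comparison of interest is between conditions, and the same children supply the answers under all three. A Pearson chi-square on a condition-by-answer table would treat 72 answers (24 × 3) as coming from 72 different children. Its variance for a difference between conditions is then wrong unless a child's answers happen to be uncorrelated.

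The sentence reads as a between-group test. It names groups, it puts safety and blinding together with demographics (which cannot differ between conditions in the same children), and it stands beside a repeated-measures model for reading.

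At stake is the tolerability comparison of tDCS, hf-tRNS and sham. If children who report sensations tend to do so in every session, the chi-square will too seldom show a difference, and the lack of significance may be read as equal tolerability. For the blinding guesses the error may run the other way.

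**Working it through.** **Inputs from the article.** Three conditions per child, one questionnaire after each, N = 24, α = 0.05. The article gives no figure for the safety or blinding comparison. Its N comes from the primary outcome and reproduces: with f = 0.25, four repeated measurements, and an assumed correlation of 0.5 and sphericity (neither is stated), λ = 0.25² × 24 × 4 / (1 − 0.5) = 12 on 3 and 69 degrees of freedom, and power is 0.817. N = 24 is the smallest sample that reaches 80%.

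**Assumptions.** The article gives no event rates and no within-child correlation. Latent correlations from −0.45 to 0.85 are therefore examined, with a rate of 40% in every condition when there is no difference and 55/35/25% (tDCS/hf-tRNS/sham) when there is one.

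**Step 1: why pairing matters.** With common rate p and correlation φ between a child's yes/no answers, the difference between two conditions has variance 2p(1−p)(1−φ)/N. Pearson's chi-square uses 2p(1−p)/N. With three equally correlated conditions its statistic therefore behaves like (1−φ) times a chi-square on 2 degrees of freedom, and its true size at nominal 5% is approximately 0.05^(1/(1−φ)):

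- φ = 0.19: 0.05^1.235 = 2.5%
- φ = 0.33: 0.05^1.493 = 1.1%
- φ = 0.49: 0.05^1.961 = 0.3%
- φ = −0.19: 0.05^0.840 = 8.1%

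These φ values correspond to latent correlations of 0.3, 0.5, 0.7 and −0.3 at a 40% rate.

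**Step 2: simulation at N = 24** (20,000 trials per row, threshold model for correlated yes/no answers).

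| Latent r | Size, chi-square | Size, Cochran's Q | Power, chi-square | Power, Cochran's Q |
|---|---|---|---|---|
| −0.45 | 10.1% | 5.2% | 51% | 38% |
| −0.3 | 7.7% | 4.9% | 51% | 42% |
| 0 | 5.2% | 5.2% | 49% | 48% |
| 0.3 | 2.6% | 5.2% | 47% | 56% |
| 0.5 | 1.3% | 5.0% | 44% | 64% |
| 0.7 | 0.4% | 5.1% | 42% | 76% |
| 0.85 | 0.1% | 5.0% | 39% | 87% |

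At negative r the chi-square's higher power is not a gain, because its size is above 5%.

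**Step 3: blinding guesses.** With 67% answering active in every condition, the size of the chi-square is 7.9% at r = −0.3, 5.2% at 0 and 1.4% at 0.5. In the extreme case where every child names exactly one session as sham, at random, φ = −1/2. The approximation gives 0.05^(1/1.5) = 13.6%, and simulation gives 14.8%.

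**Step 4: one table, several pairings.** Suppose 12 of 24 children report an effect under one condition and 6 of 24 under another. Pearson: 48 × (12×18 − 12×6)² / (24 × 24 × 18 × 30) = 3.2, p = 0.074, however the answers pair up. McNemar uses the discordant pairs, (b−c)²/(b+c):

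- 6:0 gives 6.0, p = 0.014 (exact 0.031)
- 7:1 gives 4.5, p = 0.034 (exact 0.070)
- 9:3, which is independence at these margins, gives 3.0, p = 0.083
- 12:6 gives 2.0, p = 0.157

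The same margins can therefore carry quite different evidence, and Pearson's test cannot see it.

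**The case against.** **The wording may not mean Pearson's test.** McNemar's test and Cochran's Q are also referred to a chi-square distribution, and a journal article condenses its protocol. This is fair as a caution: the between-group reading is an inference. But the article does state a method, and its wording points away from pairing, so this is more than a detail left to an analysis plan.

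**There are real groups.** This stands. Six sequences and two sham types divide the children, and a chi-square is valid for sham tDCS against sham tRNS or between sequences, including for demographics. Those comparisons do not answer how tDCS, hf-tRNS and sham differ.

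**A reader might infer that the test favours both hoped-for conclusions, safety and blinding.** The documents do not support that. The safety hypothesis is explained by the absence of severe adverse events and of dropouts due to intolerance, which is a count and not a non-significant test. For blinding, a child who knows that one of the three sessions is sham may answer in a negatively dependent way, and the chi-square then over-rejects, which works against the hypothesis. Whether children know this is itself an inference.

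**A paired test is not always more powerful.** This stands for exact McNemar. At assumed rates of 60% and 30% with φ = 0.3, power is 57% for exact McNemar, 60% for chi-square and 68% for mid-p McNemar. At 20% and 5%, exact McNemar has about 15% against 31 to 37% for chi-square. Cochran's Q gains nothing at zero correlation. The fix below therefore uses mid-p and not the exact test.

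**Conclusion.** The point holds in a limited form. The named analysis does not respect the pairing that the design creates, and a Pearson chi-square across conditions gives invalid p-values in either direction.

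Under positive within-child correlation it is conservative. At latent correlations of 0.3 to 0.7 it loses about 9 to 34 points of power against Cochran's Q, and this leans towards a no-difference reading of the tolerability comparison. Under negative correlation, which is possible for blinding guesses, it rejects too often. At zero correlation nothing is lost. These sizes rest on assumed rates and correlations.

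The primary outcome, the sample size and the safety hypothesis as the article defines it do not depend on this test. The rating is should-fix.

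**What to change.** Replace the chi-square sentence in the statistical section with text that provides for the following:

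- **Each adverse effect (any versus none) and the active/not-active guess:** Cochran's Q across the three conditions, followed by mid-p McNemar tests for tDCS versus sham, hf-tRNS versus sham and hf-tRNS versus tDCS.
- **The 0-3 severity score:** Friedman's test, followed by Wilcoxon signed-rank tests for the same pairs.
- **Estimates:** paired risk differences with 95% confidence intervals, so that a non-significant result is not read as equality.
- **Chi-square:** only for comparisons between different children (sham tDCS versus sham tRNS, or sequence groups). Demographics are not compared between conditions.

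The cost is one paragraph of analysis text. The data, the visits and the number of children stay the same, and the change can be made before unblinding.

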### Reading tasks

Four different reading tasks (text – TEXT; high-frequency words – HF; low-frequency words – LF; non-words – NW) will be presented to the participants in the Italian language. Participants will be required to read aloud as quickly and accurately as possible.

TEXT derived from an Italian novel (65). Items in HF list and LF list were matched for Italian written word frequency, number of letters and syllables, bigram frequency (according to CoLFIS)^1^ and mean onset reaction time. To avoid the repetition effect, multiple versions of each reading task will be administered. This will include different versions presented at baseline (before stimulation) and during each stimulation session, resulting in a total of six versions across the study. The purpose of this approach is to minimize the impact of task familiarity. To control for the influence of fatigue, the order of the reading tasks will be counterbalanced between the three conditions (tDCS, hf-tRNS, and sham).

Regarding reading task characteristics, each TEXT will be composed of approximately 400 syllables, each list of HF will be composed of 30 high frequency words (over 70 syllables long), each list of LF will be composed of 30 low frequency words (over 70 syllables long), and each list of NW will be composed of 30 non-words (over 70 syllables long).

For each reading task (TEXT, HF, LF, and NW), both reading speed and accuracy will be measured and considered. Concerning TEXT reading accuracy, an error point will be assigned in presence of substitution, omission, and/or addition of syllables. A 0.5 error will be assigned in case of auto-correction during reading. The number of words correctly read will be considered, and the percentage of accuracy will be calculated via dividing the number of correctly read stimuli by the total number of stimuli presented and multiplying the result by 100. For the remaining tasks (HF, LF, NW), an error point will be assigned in presence of substitution, omission, and/or addition of syllables, while auto-corrections during reading will not be treated as errors. The number of errors will be considered, and the percentage of errors will be calculated via dividing the number of errors by the total number of stimuli presented and multiplying the result by 100.

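### The primary RM-ANOVA has no session term although the design is a six-sequence crossover, which costs power for active versus sham, and practice is confounded with the Day 0 level

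*Protocol article*

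**What the plan says.** Under 'Study design', after recruitment "participants will be allocated to one of six possible combinations of conditions (i.e., ABC, ACB, BAC, BCA, CBA or CAB"). The same section states that "The ordering of conditions will be counter-matched among participants". The allocation method it names works on child characteristics: "Stratified randomization will use the minimal sufficient balancing method to prevent imbalances in baseline characteristics", with the factors listed as "participants’ demographics (e.g., age, IQ, and gender) and the severity of DD". No number of children per sequence is given. Day 0 is the screening and baseline visit, so it precedes the three sessions for every child.

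Under 'Statistical analyses and expected results', each reading measure is analysed by RM-ANOVA "with conditions (Day 0, A, B, C) as a within-subjects factor and age as covariate". The model has no term for session or sequence. Practice is dealt with in a separate, age-adjusted step: "a preliminary analysis to test the effect of the four repetitions (Day 0, Day 1, Day 2, and Day 3) of the reading tasks". The text does not say what follows if that test shows an effect.

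'Reading tasks' tackles practice by design: "To avoid the repetition effect, multiple versions of each reading task will be administered", six in all, piloted for comparable difficulty in typically developing readers. 'Withdrawal of subjects and intervention modifications' excludes children who withdraw during the intervention phase and refers to replacements, without saying which sequence a replacement takes.

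**The concern.** The three sessions form a three-period crossover. Its obvious nuisance effect is change from visit to visit, and the plan recognises this by testing for it. The effect is then left out of the model that yields the primary result. Two consequences follow.

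- **Active versus sham.** If the sequences are balanced, session effects average out of the condition means but remain in the residuals. The standard error is then too large and power is lost. If sequence counts end up unequal, part of the session effect also enters the contrast as random error.
- **Day 0.** It is a level of the analysed factor and never changes position. Any practice gain therefore appears as a difference between Day 0 and all three sessions, and so feeds the omnibus F test. Sequence balance cannot remove this, and neither can a session term.

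The primary question is whether either stimulation beats sham. The omnibus test, for which the sample size was calculated, can reject for a reason unrelated to stimulation, while the contrast of interest loses precision that could be kept at almost no cost.

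**Working it through.** **Inputs from the protocol:** 24 children, alpha 0.05, f = 0.25, four levels, six sequences.

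**Assumptions (not in the protocol):** within-child correlation 0.5, total SD 1, sphericity, and a linear practice gain of d SD per visit starting from Day 0. The protocol gives no practice figure, so d is varied from 0 to 0.5.

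**1. The plan's own figure.** The noncentrality is f² × N × m / (1 − rho) = 0.0625 × 24 × 4 / 0.5 = 12 on 3 and 69 df, giving power 0.817. With 23 children it is 0.797. The stated 24 is reproduced.

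**2. Variance of active minus sham, balanced sequences.** Without practice the variance of a child's difference is 2 × (1 − 0.5) = 1. Over the six orders, the gap in position between an active condition and sham is −2, −1, −1, 1, 1, 2. Its mean is 0, so there is no bias. Its mean square is (4 + 1 + 1 + 1 + 1 + 4) / 6 = 2. Without a session term the difference therefore appears to have variance 1 + 2d², and the standard error is √((1 + 2d²)/24).

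**3. Power for an assumed 0.5 SD effect**, two-sided paired test, 23 df:

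| d per session | Apparent variance | Standard error | Power, no session term | Power, session term |
|---|---|---|---|---|
| 0 | 1.00 | 0.204 | about 65% | 66-67% |
| 0.1 | 1.02 | 0.206 | about 64% | 66-67% |
| 0.2 | 1.08 | 0.212 | about 62% | 66-67% |
| 0.3 | 1.18 | 0.222 | about 57% | 66-67% |
| 0.5 | 1.50 | 0.250 | about 49% | 66-67% |

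The power figures come from simulation. A noncentral t calculation with noncentrality 0.5 / standard error agrees to within about one percentage point. The session-term model has 72 − 24 − 2 − 2 = 44 error df.

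**4. The plan's own post hoc test.** For Tukey's test on the RM-ANOVA residual, with both active effects at 0.6 SD and balanced sequences, simulated power for active tDCS versus sham is 0.62 / 0.62 / 0.60 / 0.56 / 0.46 at the same values of d. The residual mean square rises by the factor 1 + (2 × 24 × d²) / (69 × 0.5), which is 1.01, 1.06, 1.13 and 1.35 at d = 0.1, 0.2, 0.3 and 0.5.

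**5. False positives, active versus sham.** With balanced sequences the nominal 5% paired test rejects in about 4.8% / 4.2% / 3.7% / 1.7% of null trials at d = 0.1 / 0.2 / 0.3 / 0.5 (6,000 runs each), so it is conservative. Under simple randomisation over six sequences, a worst-case stand-in and not the protocol's method, it rejects in 4.6% to 5.4%.

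**6. Unequal sequences, same worst case.** The chance shift in a single trial has mean 0 and SD d × √(2/24) = 0.289d, that is 0.03 / 0.06 / 0.09 / 0.14 SD.

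**7. Day 0.** With balanced sequences and no stimulation effect, the four expected means are 0, 2d, 2d, 2d. Their squared deviations sum to 3d², so the omnibus noncentrality is 24 × 3d² / 0.5 = 144d² before error inflation: 1.44, 5.76, 12.96 and 36. Simulated rejection is about 14% / 44% / 80% / over 99%, even with exactly four children per sequence.

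**The case against.** The strongest reply is that the design already handles practice. Six piloted versions of each task are used and the order of conditions is counter-matched, so practice may be close to zero. At up to 0.2 SD per session the power loss is only about three percentage points. This stands: the loss for active versus sham is small unless practice reaches roughly 0.3 SD per session. Alternate versions limit repetition of items, though, and do not exclude growing familiarity with the task and setting.

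A second reply is that an article leaves detail to the full protocol. That holds for the mechanics of allocation. It does not cover the model, whose terms are stated here.

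Three stronger readings are tempting, and the documents do not support them.

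- **That allocation ignores the sequences and so biases active versus sham.** The protocol states counter-matching as its intent. What is missing is a number per sequence and a rule for replacements. Figures from pure chance allocation, such as four per sequence in only 0.06% of draws, describe simple randomisation and not this trial. Any imbalance would average zero over trials.
- **That false claims against sham become more likely.** Step 5 shows an error rate at or below nominal.
- **That balancing on age, IQ, gender and severity is pointless.** Main effects of such traits cancel within a child, but the Discussion names age and gender as sources of variability in stimulation effects, and effect modifiers do not cancel.

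It could also be said that dropping Day 0 from the factor departs from the primary outcome, which is defined against Day 0. It does not alter the contrast: each child has one Day 0 score, so (active − Day 0) − (sham − Day 0) = active − sham.

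**Conclusion.** The point holds as a matter of efficiency and of which test carries the conclusion. It is not a finding of bias against sham. Omitting session makes the active-sham test conservative. The cost ranges from negligible to roughly 17 percentage points of power (about 66% down to 49%) as assumed practice goes from 0 to 0.5 SD per session. The confounding of practice with Day 0 is the more consequential part: an assumed 0.1 SD per session is enough to raise omnibus rejection to about 14% with no stimulation effect. A significant omnibus test, or a gain over Day 0, therefore cannot be read as a stimulation effect.

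The sizes depend on correlation 0.5, sphericity, linear practice that includes the step from Day 0 to Day 1, and the assumed effects of 0.5 or 0.6 SD. The direction does not depend on the particular values. The change should be made, but the trial is not invalid without it.

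**What to change.** **Analysis.** Analyse the three stimulation sessions in a mixed model with fixed condition, fixed session (Day 1, 2, 3) and age, and random child. Fit it whatever the preliminary repetition test shows, and keep that test as description only. Base primary inference on active versus sham across Days 1-3, not on an omnibus test that includes Day 0.

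**Allocation.** Give effect to the counter-matching by stating equal numbers per sequence, four each at 24, and by having a replacement child take the withdrawn child's sequence. Balancing on age, IQ, gender and severity may stay as a secondary aim. Enrolment began in August 2023, so four per sequence is reachable only if allocations so far allow it. If they do not, the session term adjusts for the remaining imbalance.

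**Cost.** The session term takes two degrees of freedom (46 to 44), and the changes need a short amendment. No extra children are needed for the session term. The sample-size paragraph would need rewording, because it sizes the four-level omnibus test, which would no longer be primary. With the same f and correlation, a three-level test has noncentrality 0.0625 × 24 × 3 / 0.5 = 9 and power of about 0.74 at 24 children, and the amendment should say so openly.

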### Clinical eligibility

The inclusion criteria will be as follows: (1) right-handed Italian-native speakers of both genders, who have been diagnosed with DD based on the Diagnostic and Statistical Manual of Mental Disorders, Fifth Edition [DSM-5; (1)] and national recommendations. Their assessment will be conducted by experienced psychologists and neuropsychiatrists using “gold standard” assessment tools (45–48) and considering their developmental history; (2) intelligence quotient (IQ) ≥ 85; (3) age between 8 years and 13 years and 11 months; and (4) normal or corrected-to-normal vision; (5) normal auditory capabilities.

The exclusion criteria will be as follows: (1) presence of another primary psychiatric diagnosis (e.g., depression, anxiety), autism, or ADHD; (2) personal history of neurological/medical/genetic diseases; (3) personal or first-degree relatives’ history of epilepsy; (4) receiving any concomitant treatment for DD during the enrolment in the project; and (5) currently receiving any Central Nervous System (CNS)-active drug treatment.

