### Sample size

The sample size is calculated on the primary outcome by *a priori* analysis in G*Power, version 3.1.9.7 (The G*Power Team, Düsseldorf, Germany). Based on the study design and assumptions, the estimated results suggest that participants who receive a single session of active tDCS or hf-tRNS will demonstrate an improvement in TEXT reading accuracy compared to their baseline performance. On the other hand, participants who receive a single session of sham tDCS or sham tRNS are not expected to show a significant change in their performance compared to baseline. While the design of this project has never been employed in DD, we will refer to (i) a previous study by Costanzo and collaborators (16) who prove the effectiveness of a one-session active left anodal/right cathodal tDCS over temporo-parietal regions in a within-subject design; (ii) a study with similar features (e.g., one-session, sham-controlled experiment, comparing baseline vs. tDCS vs. tRNS vs. sham) assessing other cognitive functions (35).

Based on these previous results, to be cautious and conservative, we estimate a medium effect size (f) of 0.25. With an estimated *f* = 0.25, α value = 0.05 (i.e., probability of false positives of 5%), and *β* = 0.80 (i.e., at least 80% power), the sample size is 24 as calculated using a Repeated Measures-Analysis of Variance (RM-ANOVA) model with four within factors (i.e., baseline, active tDCS, active hf-tRNS, and sham).

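### Age should be left out of the RM-ANOVA condition test or centred: uncentred age crossed with condition would cut omnibus power from about 82% to about 7%

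*Protocol article*

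**What the plan says.** Under Statistical analyses and expected results, the protocol article specifies one RM-ANOVA per reading measure, "with conditions (Day 0, A, B, C) as a within-subjects factor and age as covariate". This covers the primary outcome (text reading accuracy) and the seven secondary reading measures. The same section adjusts for age in a preliminary test of repetition over Days 0 to 3. It also names Mauchly's test, the Greenhouse-Geisser correction, Tukey post hoc comparisons and partial eta squared. It does not say whether age is centred or whether an age-by-condition term is fitted.

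Under Sample size, the authors write "we estimate a medium effect size (f) of 0.25". The number needed is described "as calculated using a Repeated Measures-Analysis of Variance (RM-ANOVA) model with four within factors", by which they mean a baseline and the three stimulation sessions. The result is stated in these words: "i.e., at least 80% power), the sample size is 24". No covariate appears there.

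Clinical eligibility sets "age between 8 years and 13 years and 11 months".

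**The concern.** Age is a property of the child, not of the session. An age effect that is the same in all four conditions drops out of every difference between conditions, so adjusting for it cannot make those differences more precise. The within-subject design has already removed it.

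The possible harm lies in how a covariate is commonly handled in the multivariate form of repeated-measures ANOVA, which the named sphericity test, correction and effect size suggest. In that form each within-child contrast is regressed on the between-child terms. Age is then crossed with condition automatically, and the condition test is a test of the intercepts. With age in uncentred years, the intercept is the predicted condition effect at age zero, eight years below the youngest eligible child. Its standard error is far larger than that of the effect at the average age.

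At stake is the omnibus test on which the trial was sized, for all eight reading measures. A stimulation effect of the planned size could be reported as a non-significant condition effect with a small partial eta squared. The repetition analysis could miss a real practice effect in the same way.

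**Working it through.** **Inputs.** From the article: N = 24, f = 0.25, alpha = 0.05, m = 4 repeated measurements, ages 8 to 13.92 years. Assumed, because not stated: correlation between measurements rho = 0.5, sphericity, and ages uniform over the eligible range.

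**1. Reproduce the stated sample size (no covariate).** In the G*Power within-factors form, lambda = f² × N × m / (1 − rho) = 0.0625 × 24 × 4 / 0.5 = 12, with df = (m − 1, (N − 1)(m − 1)) = (3, 69). Power is 0.817. N = 23 gives 0.797, so 24 is the smallest adequate number and the stated figure reproduces. It depends on rho: the required N would be 45 at rho = 0, 32 at 0.3, 15 at 0.7 and 11 at 0.8.

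**2. Add age, crossed with condition.** For each orthonormal contrast, d = b0 + b1 × age + error, and the condition test is the joint test of the b0 terms. The variance of b0 is (sigma²/N) × (1 + mean²/SD²), where mean and SD are those of age as entered. One error degree of freedom is lost per contrast, so the error df are (24 − 2) × 3 = 66.

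- Centred age: the mean is 0, the factor is 1, and lambda stays at 12.
- Uncentred age: mean = (8 + 13.92)/2 = 10.96 and SD = 5.92/√12 = 1.71. The factor is 1 + (10.96/1.71)², about 42, so standard errors rise by √42, about 6.5 times, and lambda = 12/42.2 = 0.28.

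**3. Power of the omnibus condition test at N = 24.**

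| Model | lambda | df | Power | Simulated (20,000 runs) |
|---|---|---|---|---|
| No covariate | 12 | 3, 69 | 0.817 | 0.821 |
| Age centred, crossed | 12 | 3, 66 | 0.816 | 0.821 |
| Age uncentred, crossed | 0.28 | 3, 66 | 0.066 | 0.066 |

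With uncentred age, about 921 children would be needed for 80% power.

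**4. Sensitivity of the uncentred result.** For mean ages of 10 to 11.5 and SDs of 1.0 to 2.0, power runs from 0.055 to 0.077. At the uniform age distribution, a higher correlation helps little: power is 0.078 at rho = 0.7, 0.093 at 0.8 and 0.141 at 0.9.

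**5. Error rate.** With no effect at any age, the uncentred test keeps its level (0.049). Suppose instead that the average effect is zero but changes by 0.15 SD per year of age (10,000 runs). The uncentred test then rejects in 26% of trials, against 6% when centred, because it addresses the effect at age zero and not the average effect.

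**6. Comparisons at mean age.** Evaluating the fitted contrast at the mean age returns the variance to sigma²/N. A pairwise comparison made there has a factor of 1 and loses only the degree of freedom.

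**The case against.** The strongest reply is that the article never says age is uncentred, gives no age-by-condition term and names no analysis software. The one program named, in "analysis in G*Power, version 3.1.9.7", serves the sample size. Centring is a coding detail that a condensed article may leave to the full protocol or analysis plan. All of this stands, and it makes the loss conditional. A reader might infer that the plan as written will lose its power. The article does not support that, since an additive or centred age term satisfies its wording equally well and costs essentially nothing.

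A reader might also infer that age can never sharpen a within-child contrast. That is too absolute. The Discussion gives age as a possible source of variability in the response to stimulation. If the effect changes by 0.3 SD per year, centred age crossed with condition raises omnibus power from 0.711 to 0.777. The cancellation holds only for an age effect common to all conditions.

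Finally, a reader might infer that the active-versus-sham comparisons lose their power too. The article assigns pairwise questions to Tukey comparisons. It does not say that these are made at age zero, or that they require a significant omnibus result. Made at mean age, they are unaffected.

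The reply does not remove the point. Entering age is a positive choice in the analysis section that the sample-size section did not plan for, and in a common fitting routine it would defeat the test on which the trial was sized.

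**Conclusion.** The point holds as a conditional risk to the omnibus condition test and its partial eta squared in all eight reading measures, and to the preliminary repetition test. Two conditions are needed: age in uncentred years, and a routine that crosses it with the within-subject factor. If both are met, the power that the article sets at 80% or more falls to about 7%. That conclusion does not hinge on the assumed age distribution, and power would still be only about 14% at a correlation of 0.9. If either condition fails, the loss is nil. The documents do not show which case applies, so this is not a demonstrated error. It is worth settling before the analysis because the protection is nearly free.

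**What to change.** Choose one of two lines for the analysis section:

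- omit age from the primary condition test; or
- enter age centred at the sample mean, state that the condition effect is evaluated at that mean, and report condition-by-age separately as an exploratory moderator.

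Apply the same line to the preliminary repetition analysis, and state that Tukey comparisons are made at mean age if age is kept.

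Omitting age costs nothing in the sizing model. Centring costs one error degree of freedom per contrast (69 to 66 in total) and moves omnibus power from 0.817 to 0.816. The sample size need not change.
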